## Methods

### Trial design

This will be a multicenter, open-label, prospective RCT. Elderly patients will be included from seven centers, including Shenzhen People’s Hospital affiliated to Jinan University, West China Hospital affiliated to Sichuan University, The Affiliated Hospital of Guizhou Medical University, Taihe Hospital affiliated to Hubei University of Medicine, The Third Affiliated Hospital of Kunming Medical University, Sichuan Provincial People’s Hospital, and Henan Provincial People’s Hospital. All participants provided their written informed consent to participate in a RCT that examined the effects of low-level MAP (60–70 mmHg) vs. high-level MAP (90–100 mmHg) in elderly patients (aged 65 years or more) during non-cardiothoracic surgery under GA (trial registered at ClinicalTrials.gov under registration number: NCT02857153). MAP was calculated from the standard equation MAP = (2/3) diastolic blood pressure (DBP) + (1/3) systolic blood pressure (SBP) (in mmHg). We hypothesize high-level BP of the intervention for reducing the incidence of postoperative complications.

This study protocol was written in accordance with the Standardized Protocol Interventions: Recommendations for Interventional Trials (SPIRIT) 2013 Statement (see Additional file 1 for the completed SPIRIT checklist) [21]. The time schedule of enrollment, assessment, interventions, and follow-up according to SPIRIT guidelines can be found in Fig. 1.

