### Patient population and eligibility criteria

Patient eligibility is assessed at the preoperative anesthesia consultation. All eligible patients must sign a specifically designed informed consent form.

Inclusion criteria are: men and women; American Society of Anesthesiologists (ASA) I–II; aged 65 years or more; scheduled to undergo non-cardiothoracic surgery with GA; and 2 h or more of scheduled surgery time.

Participants will be excluded if they meet any of the following conditions: (1) the patient suffered from cardiovascular disease and metabolic diseases, such as hypertension, cardiac diseases, diabetes; (2) the patient has severe liver, kidney, or blood disease; (3) the patient is accompanied severe cognitive impairment (Mini-Mental State Examination [MMSE] score < 15) [22]; (4) preoperative history of schizophrenia, epilepsy, parkinsonism, use of cholinesterase inhibitor, or levodopa treatment; use of haloperidol or other neuroleptics during or after anesthesia; (5) neurosurgery; (6) individuals unlikely to survive for > 24 h; (7) previous participation in this study.

Trial schematic diagram is shown in Fig. 2.

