### Statistical analysis

Postoperative delirium is a frequent complication after major surgery in elderly patients and is related to an increase in mortality [31]. Probability of first postoperative day PD in elderly hip fracture patients is in the range of 20–60% [9]. PD occurred in 44% of elderly patients after a major operation [31]. Our sample size was calculated to detect a 15% difference in PD between the two groups with a two-tailed test, a significance level (alpha) of 5%, and a power of 80%. The sample size calculation was performed on STATA 14.0 software (StataCorp, College Station, TX, USA). We plan to include a total of 322 participants.

Analyses will be conducted at the Clinical Research Institute of Shenzhen People’s Hospital by blinded biostatisticians. Data analysis is on an intention-to-treat basis.

The level of significance was set at 5% and statistical analysis was performed using GraphPad Prism version 6.02 for Windows (GraphPad Software, San Diego, CA, USA). Continuous variable will be summarized using means and SDs (normally distributed data) or medians and ranges (non-normally distributed data). We will perform group comparison by using the Student’s t test or Mann–Whitney test for quantitative variables and Pearson’s chi-squared test for categorical variable. The odds ratio and 95% confidence interval will be computed with logistic regression.

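### The chi-squared test named for delirium is valid and meets its planned power, but it uses no baseline information, and the only effect measure named is an odds ratio although the target is an absolute difference

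*Protocol article*

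**What the plan says.** The Statistical analysis section names Student's t or Mann–Whitney for quantitative variables and Pearson's chi-squared for categorical ones. It then adds: "The odds ratio and 95% confidence interval will be computed with logistic regression". It lists no covariates for that model and does not say that the model contains arm alone. It does not say whether the chi-squared test or the model is the primary comparison.

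The same section gives the planning target: "Our sample size was calculated to detect a 15% difference in PD between the two groups", two-sided at 5% with 80% power, and "We plan to include a total of 322 participants". It cites the rate behind this as background: "PD occurred in 44% of elderly patients after a major operation". No risk difference with a confidence interval is named.

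On the population, Trial design says "Elderly patients will be included from seven centers", and the Discussion acknowledges that procedures and clinical settings vary. Eligibility starts at 65 years with no upper limit. On cognition it excludes only severe impairment: "the patient is accompanied severe cognitive impairment (Mini-Mental State Examination [MMSE] score" below 15. Randomization and blinding describes 1:1 blocked allocation and names no stratification factor. Data collection lists date of birth but not the MMSE score. Trial status reports 60 patients recruited by 1 November 2016.

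**The concern.** Two separate choices are at issue.

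**Precision.** A chi-squared test cannot use baseline information. Center and age are on file for every patient and may predict delirium. The sample size carries no visible margin, since it reproduces without any allowance for dropout. If these variables are prognostic, the analysis gives up power that would cost almost nothing to keep.

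**Scale.** The trial was planned around an absolute difference in incidence, yet the one effect measure promised is an odds ratio. Delirium is expected in roughly 30–45% of patients. At such rates the odds ratio lies further from 1 than the risk ratio and does not by itself tell a clinician how many patients avoid delirium. If covariates do enter the model, the odds ratio also depends on which ones, and none is fixed.

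**Working it through.** **1. Reproduce the sample size.** Inputs from Statistical analysis: two-sided alpha 5%, power 80%, difference 15 points, N = 322. The 44% reference rate is cited there but not declared as the design rate; I infer it because it reproduces N.

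n per arm = [1.960·√(2·p̄·(1−p̄)) + 0.842·√(p1(1−p1) + p2(1−p2))]² / (p1−p2)²

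With p1 = 0.44, p2 = 0.29 and p̄ = 0.365:
- 2·0.365·0.635 = 0.46355, square root 0.681
- 0.2464 + 0.2059 = 0.4523, square root 0.673
- n = (1.334 + 0.566)² / 0.0225 = 160.5, so 161 per arm and 322 in total

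Power at 161 per arm is 80.1%. This is the sample-size formula for the chi-squared test, so test and sample size agree. Other readings do not give 322: 44% vs 59% gives 348, 60% vs 45% gives 346, 40% vs 25% gives 304, and 44% vs 29% with continuity correction gives 348.

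**2. Is the odds-ratio scale underpowered?**
- OR = (0.29/0.71)/(0.44/0.56) = 0.52, so |log OR| = 0.654
- SE = √[(1/0.2464 + 1/0.2059)/161] = √(8.915/161) = 0.235
- Power = Φ(0.654/0.235 − 1.960) = Φ(0.82) = 79.4%

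That is 0.7 points below 80.1%. At the design point, the 15-point difference and OR 0.52 are the same alternative.

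**3. How the odds ratio reads.** RR = 0.29/0.44 = 0.66, a 34% relative reduction; the OR of 0.52 looks like 48%. Nor does the OR fix the absolute effect across the 20–60% range that the section cites:
- Reference 20%: odds 0.25 × 0.52 = 0.13, risk 11.5%, difference 8.5 points
- Reference 60%: odds 1.5 × 0.52 = 0.78, risk 43.8%, difference 16.2 points

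**4. What adjustment could add.** The documents give no prognostic strength for age, MMSE or center, so these are assumptions. The simulation used 161 per arm, marginal rates held at 44% vs 29%, seven centers, independent age and MMSE, and 5,000 runs per row. Monte Carlo error is √(0.8·0.2/5000), about 0.6 points. The adjusted test is the Wald test of arm in a logistic model with age, MMSE and center.

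| Assumed OR per SD (age and MMSE, each) | Center SD (log-odds) | Chi-squared power | Adjusted power | Conditional OR for arm |
|---|---|---|---|---|
| 1.0 | 0 | 81.3% | 80.7% | 0.52 |
| 1.3 | 0.2 | 79.6% | 80.5% | 0.51 |
| 1.5 | 0.3 | 79.6% | 82.8% | 0.49 |
| 2.0 | 0.5 | 80.3% | 87.5% | 0.45 |
| 2.5 | 0.5 | 79.5% | 89.2% | 0.41 |

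The unadjusted test stays near 80% throughout. The gain runs from none to about 10 points (89.2 − 79.5 = 9.7). With no prognostic effect the cost is 0.6 points, about the size of the simulation error. The last column shows the same 15-point difference appearing as an OR anywhere from 0.52 to 0.41, depending on how prognostic the covariates are. These rows include MMSE; with center and age alone, any gain would be smaller.

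**The case against.** The strongest reply is that nothing here is wrong. An unadjusted chi-squared test in a randomized trial controls its error rate, its confidence interval already allows for chance imbalance, and it matches the formula that gives 322. All of this stands: adjustment would improve the plan, not repair an error. Entry is also limited to ASA I–II without hypertension, cardiac disease or diabetes, so strong prognostic differences cannot be taken for granted.

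Three stronger readings are tempting, and the documents do not support them.

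- A reader might infer that the odds ratio comes from an unadjusted model. The text says only that logistic regression will be used, and a covariate list is something an article may leave to a fuller plan.
- A reader might infer that the trial reports on a scale it was not powered for. Chi-squared tests the difference in proportions on which the trial was sized, and power on the log-odds scale is 79.4%. The scale point concerns interpretation.
- A reader might infer that the analysis must include center because randomization was stratified by it. No stratification factor is stated.

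It is also fair to object that MMSE cannot be assumed available. It appears only as an exclusion threshold and is absent from the list of collected data.

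What survives is what the article does fix: a test that takes no covariates for the primary outcome, and an odds ratio as the only named effect measure against an absolute target.

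**Conclusion.** The point holds as a worthwhile improvement in method. The planned test is valid and delivers its 80%. A pre-specified adjusted analysis with a risk difference would serve the trial's own target better at almost no cost.

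The scale point is firm given 44% vs 29%, which is inferred from the reproduced sample size: OR 0.52 against RR 0.66. The power point is conditional. The gain lies between none and about 10 points under assumed prognostic strengths that include MMSE. Any single figure within that range, such as a rise from 80% to 85%, reflects one chosen scenario and cannot be derived from the documents.

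**What to change.** In Statistical analysis, name one primary analysis: a logistic regression of seven-day delirium on arm, with center and age (continuous) as pre-specified covariates. Add the baseline MMSE score only if it is confirmed as recorded for all patients, including the 60 enrolled by 1 November 2016. State that the arm term carries the two-sided 5% test.

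Report the standardized (marginal) risk difference with 95% CI as the primary estimate, next to the two arm incidences. Give the odds ratio as supportive and label it as adjusted. Keep Pearson's chi-squared as a sensitivity analysis.

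The model is small enough for the data. At the planning rates about 322 × 0.365 ≈ 118 patients would have delirium, against eight terms besides the intercept (arm, six center indicators, age), or about 15 events per term. A rule for combining very small centers should be fixed in advance. The section names GraphPad Prism for the analysis and STATA for the sample size, so the plan should also name the package that will fit this model.

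For center and age the cost is wording plus slight extra analysis work; for MMSE it also requires a check of existing records. If the covariates turn out not to be prognostic, the price is about half a point of power. Sample size, allocation and patient care do not change. The change should be made before any comparison by arm is seen.

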### Trial oversight

A Trial Management Group including the Chief Investigator, Trial Coordinator, Trial Manger, Data Manager and Trial Statistician are in contact weekly.

A Trial Steering Committee (TSC) will meet at least three times each month over the Internet, and more frequently if required, to review the trial progress and to ensure that it is being conducted in accordance with the protocol, relevant regulations, and the principles of good clinical practice.

A DSMC will review trial progress and safety data. The DSMC is independent of the trial investigators and will comprise three independent members including two clinical specialists and a trial statistician.

### Protocol amendments

Protocol amendments will be agreed upon with the TSC, DSMC, Sponsor and Funding Body before submission for ethical approval. Following ethical approval, protocol modifications will be communicated with relevant parties such as the trial investigators, the trial registry, and, if required, trial participants.

### Dissemination policy

The results of the trial will be widely disseminated to patients, health professionals, commissioners, policy makers, and the general public. Our patient public involvement members will play a key role in this. The trial results will be disseminated to a wide clinical audience through publication in a high impact international scientific journal.

## Discussion

Intraoperative MAP influences clinical outcomes [8, 9, 32]. Intraoperative hypotension has been implicated in ischemia-reperfusion injury to the brain, heart, and kidneys and is associated with death [15, 17, 20]. This multicenter, open-label, randomized, parallel-controlled clinical trial is designed to test the hypothesis that, compared with low-level MAP, high-level MAP under GA reduces postoperative complications in elderly patients during non-cardiothoracic surgery. Even a neutral result will provide an important insight, as this would mean that more studies are needed to explore a safe and effective way of blood pressure management during GA in elderly patients. This is the main strength of the present study.

There are some limitations to our study protocol. First, a multicenter design is adopted so that patients enrolled in the study include a variety of surgical procedures under different clinical environments. This will increase the generalizability of our results. Because of the apparent difference between BP management, a double-blind design cannot be achieved. Therefore, we had to use an open-label design. The following measures will be undertaken to decrease the risk of potential bias. Second, there is evidence that intraoperative BP influence long-term consequences in elderly patients after GA [33]. However, our research is primarily concerned about the effects of low-level vs. high-level MAP on short-term postoperative complications. Third, patients who will be included as eligible participants should have no cardiovascular disease and metabolic diseases. Therefore, the results of this study will be restrainedly applied to all elderly patients during non-cardiothoracic surgery under GA.

Appropriate BP management would improve patient outcomes. Strengths of the protocol include that it is the first multicenter and centrally randomized study and that it observes both the primary (the seven-day incidence of PD) and secondary endpoints (duration days of PD, intraoperative urine volume, intraoperative blood loss, specific postoperative complications, and all-cause 28-day mortality). Results of the study will provide evidence for chasing felicitous BP management in elderly patients during non-cardiothoracic surgery under GA.

### Trial status

The trial is currently recruiting participants. To date (1 November 2016), 60 participants have been recruited. A report releasing study results will be submitted for publication in an appropriate journal, approximately 15 months after finishing data collection.

## Abbreviations

ALT: Alanine aminotransferase
APTT: Activated partial thromboplastin time
ASA: American Society of Anesthesiologist
AST: Aspartate transaminase
BIS: Bispectral index
BNP: Brain natriuretic peptide
BP: Blood pressure
BUN: Blood urea nitrogen
CAM-ICU: Confusion assessment method for the intensive care unit
CK: Creatine kinase
CK-MB: Creatine kinase isoenzymes
CREA: Serum creatinine
CRP: C-reactive protein
CT: Computed tomography
DBP: Diastolic blood pressure
DSMC: Data Safety and Monitoring Committee
GA: General anesthesia
HB: Hemoglobin
INR: International normalized ratio
IRB: Institutional Review Board
KDIGO: Kidney Disease, Improving Global Outcomes
MAP: Mean arterial pressure
MMSE: Mini-Mental State Examination
P: Pulse
PaCO2: Arterial carbon dioxide pressure
PaO2/FiO2: Oxygenation index
PCIA: Controlled intravenous analgesia
PD: Postoperative delirium
PLT: Platelet
PT: Prothrombin time
R: Respiratory rate
RASS: Richmond Agitation Sedation Scale
RCT: Randomized controlled trial
SBP: Systolic blood pressure
SPIRIT: Standard Protocol Items, Recommendations for Interventional Trials
TSC: Trial Steering Committee
WBC: White blood cell
